**Figure 3 F3:**
[figure not shown]
Identification of Group 6.

GROUP 1: Patients of all ages with existing cardiovascular disease or diabetes, whose blood pressure or cholesterol level is outside the QOF target range at the last estimation, or no "in date" level is recorded.

GROUP 2: Patients who are not known to have cardiovascular disease or diabetes, are *under *75 yrs old, and whose risk profile is incomplete – more information is required to perform a risk estimate – but whose cardiovascular risk would be greater than 20% if the "assumed" values of the missing factors are used (see definition in appendix).

GROUP 3: Patients who are not known to have cardiovascular disease or diabetes, are *under *75 yrs old, and whose most recent risk variable values indicate that their risk level is raised.

GROUP 4: Patients who are not known to have cardiovascular disease or diabetes, are *greater than *75 yrs old and who have persistently elevated blood pressure based on the three most recent consecutive readings.

GROUP 5: Patients with possible undiagnosed diabetes on the basis of at least one previous high blood glucose record.

GROUP 6: Patients with CVD but not diabetes, who have not had a blood glucose measurement in the past three years.

Information on the "intervention" patients identified at each search is revealed to the practices. Information on the control patients including the number identified will be saved but no action will be triggered (Figure 4).

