• Group 3 patients: ***This patient's estimated cardiovascular risk may be elevated, based on the most recent risk variable values.(State assumptions made)***

• Group 4 patients: ***This patient's blood pressure is persistently elevated based on three consecutive values*.**

• Group 5 patients: ***This patient may have undiagnosed diabetes, based on a previous raised blood glucose level ≥ 11.1 mmol/L***.

• Group 6 patients: ***This CHD/Stroke patient (state which) has no recorded blood glucose measurement in the past three years***.

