### Secondary outcomes

• Difference in the proportion of high risk patients (Groups 1, 3 and 4) identified in the control and intervention populations averaged over the last three searches in the two year intervention period, and in the third year following the end of the intervention.

• Difference in the proportion of patients in each population identified with missing data (Groups 2 and 6) averaged over the last three searches in the two year intervention period, and in the third year following the end of the intervention.

• Difference in the proportion of patients with undefined diabetes status (i.e. raised blood glucose levels with no diagnosis of diabetes and no FBG or OGTT results to confirm status) (Group 5) in the intervention and control populations averaged over the last three searches in the two year intervention period, and in the third year following the end of the intervention.

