**Table 2 T2:** 

Currently registered patients:	12,245
Plasma glucose on record ≥ 11.1 mmol/L but no diagnosis of diabetes	6

Of these six:

1. Four patients had undiagnosed type 2 diabetes later confirmed by fasting blood glucose measurements.

2. One patient had impaired fasting glycaemia (FBG 6.9 mmol/L) and is awaiting further investigation with OGTT to exclude diabetes.

3. One patient had probable steroid induced hyperglycaemia and has had a normal blood glucose value recorded since stopping the steroids.

We are therefore including as part of the regular searches a query to identify such patients, who may have undiagnosed diabetes based on previous raised measurements. Such patients identified in this study will need to have a subsequent non-diabetic fasting blood glucose level (≤6.9 mmol/L) or Oral Glucose Tolerance Test in order that future searches classify them as not having diabetes (see also appendix 5 below). Some of these patients in whom diabetes appears to be refuted by fasting measurements may go on to have further abnormal plasma glucose levels, in which case they will again be identified as possible cases (Group 5) until a further normal fasting glucose level is obtained, or a diagnosis of diabetes is made.

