### 3. Screening for type 2 diabetes in populations at risk of CVD

Diabetes UK has issued a position statement on the early identification of people with type 2 diabetes [46]. Among other groups, this document identifies people with ischaemic heart disease, cerebrovascular disease, peripheral vascular disease or hypertension as high risk groups justifying screening, with a screening interval of three years. However a reliable and practical screening test has not been established. Whilst fasting plasma glucose estimation is significantly more specific than random plasma glucose estimation, it is less practical. In addition to the detection of possibly undiagnosed patients described above, we have therefore designed the study to encourage blood glucose testing at least every three years in groups who either have, or who are at high risk of CVD. These tests can be carried out during the routine blood checks that patients receive for monitoring of lipid lowering or anti-hypertensive therapies. Therefore negative diabetes status will only be assumed if the patient is not on the Diabetes register *and *a normal plasma glucose level (random or fasting) is present in the record within the three years prior to the search. We will be allowing the follow up of patients with borderline plasma glucose levels to remain at the discretion of the practices. (The recently published Joint British Societies guidelines on prevention of cardiovascular disease in clinical practice (JBS 2), clarifies currently recommended practice in this area for the first time [4].) This study may be able to determine whether this approach is useful as a means of detecting type 2 diabetes earlier in these groups, given its practicality and low cost. Practices are at liberty to use more specific screening tests on any individual whom they feel justifies it.

### 4. Search groups 1, 3 and 4

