8. Diabetes status, according to whether or not the patient is on the Diabetes register. However, as discussed above, this depends on the quality of such registers. If a primary prevention patient less than 75 yrs does not have a diagnosis of diabetes, but there is no blood glucose level "in date" (i.e. in the past three years), then the risk algorithm will base the risk calculation on an assumption of *positive *Diabetes status, and if the risk level is then high, the practice will be notified with this assumption stated, as a Group 2 Alert message. If a patient (this time including those above 75 yrs) is not on the Diabetes register but there is a record of a blood glucose level greater than or equal to 11.1 mmol/L, then the practices will be notified for clarification, regardless of the patient's CHD/Stroke status or calculated risk level as a Group 5 patient. The matter can be clarified by the practice teams if they wish, by organising a Fasting Blood Glucose (FBG) or Oral Glucose Tolerance Test (OGTT). A FBG ≤6.9 mmol/L or OGTT code following (at a later date to) the high random blood glucose level will mean that the patient is no longer in Group 5 (but may re-enter it if further raised blood glucose levels occur). The FBG or OGTT must be clearly recorded electronically by the practices using appropriate codes (to distinguish fasting values from random blood glucose values), or the patient will continue to be flagged up in subsequent searches. If, despite a normal FBG result or OGTT, a *further *raised random value subsequently occurs (≥ 11.1 mmol/L) then once again the program will question whether or not the patient has diabetes by including them in Group 5, until a *further *FBG ≤ 6.9 or OGTT code is recorded, or the patient is diagnosed and added to the Diabetes register.

5c "**Assumed values**" for the missing variables means:

1. For systolic blood pressure: Male 135 mmHg, Female 132 mmHg

2. For total serum cholesterol: Male 5.7 mmol/L, Female 6.2 mmol/L

3. For HDL cholesterol: Male 1.4 mmol/L, Female 1.7 mmol/L

4. For diabetes: positive status.

5. For smoking status: non-smoker.

These blood pressure and cholesterol thresholds are the approximate median or mean values in the 50–74 year age group taken from the Health Survey for England 2003 [49].

5d A **"cardiovascular event" **is defined as:

1. A new diagnosis of cardiovascular disease (i.e. entry onto the CHD or Stroke/TIA registers)

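### The Group 5 (undefined diabetes status) outcome mixes arm-dependent detection with arm-dependent resolution, so neither a difference nor a null result shows whether the e-Nudge clears up uncertain status

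*Protocol article*

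**What the plan says.** The third bullet under Secondary outcomes is the "Difference in the proportion of patients with undefined diabetes status (i.e. raised blood glucose levels with no diagnosis of diabetes", with the further condition that no fasting glucose or tolerance test has settled the matter. It is taken over each whole arm, "averaged over the last three searches in the two year intervention period, and in the third year following the end of the intervention".

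Group 5 is defined under Applying the search strategy as "Patients with possible undiagnosed diabetes on the basis of at least one previous high blood glucose record". Definitions 5b (item 8) sets the threshold at 11.1 mmol/L in a patient not on the Diabetes register. It lets the patient leave on a later fasting value of 6.9 mmol/L or less, a tolerance test code, or entry on the register.

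The plan intends to increase glucose testing. Appendix 3 states that "we have therefore designed the study to encourage blood glucose testing at least every three years in groups" with CVD or at high risk of it. Two prompts do this:

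- Group 6 covers "Patients with CVD but not diabetes, who have not had a blood glucose measurement in the past three years", and its alert says that the patient "has no recorded blood glucose measurement in the past three years".
- Group 2 covers patients without CVD or diabetes, under 75, with missing values. If glucose is out of date, diabetes is assumed, and "if the risk level is then high, the practice will be notified with this assumption stated, as a Group 2 Alert message".

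Under Control condition, only Group 1 alerts may reach control patients, where they are already usual care. All other alerts and lists are withheld, including those for Group 5.

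**The concern.** Entry to the numerator needs a test, and the trial prompts tests in one arm only. Take two patients with the same undetected high glucose. The intervention patient is more likely to be tested and so to enter Group 5. The control patient is more likely to remain untested, and then counts as not having undefined status. Yet Appendix 3 accepts negative diabetes status only with a normal glucose in the previous three years, so under the plan's own rule that control patient's status is not known.

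Two consequences follow.

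- A prompted Group 6 test that reads 11.1 mmol/L or more removes the patient from the missing-data outcome (a gain) and adds the patient to the Group 5 outcome (a loss).
- Detection never scores as a gain on the Group 5 outcome. A case found and left open raises the proportion. A case found and diagnosed scores the same as a patient never tested. No other listed outcome counts new diagnoses, although Appendix 3 hopes to learn whether the approach finds type 2 diabetes earlier.

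At stake is what this result can be taken to mean.

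**Working it through.** The plan gives no expected figure for this outcome, so there is none to reproduce. Its sample size concerns the primary outcome only.

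**1. Expected count.** Inputs: 6 patients with "Plasma glucose on record ≥ 11.1 mmol/L but no diagnosis of diabetes" among 12,245 registered (Table 2), and a combined list of about 70,000 (below Table 1).

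- 6 / 12,245 = 0.49 per 1,000 registered.
- 70,000 × 6 / 12,245 = 34.3 in all, about 17 per arm.

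The pilot count covers all ages. If all six patients were over 50, the over-50 share cancels and 17 per arm stands. If some were younger, the count is lower.

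**2. The two flows.**

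| Process | Prompt | Arm prompted | Effect on Group 5 proportion |
|---|---|---|---|
| New recorded high values | Group 2 and Group 6 alerts | Intervention only | Up |
| Diagnosis or clearance | Group 5 alerts and lists | Intervention only | Down |

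**3. Net ratio.** In a steady state, which simplifies a two-year trial, prevalence = inflow rate × mean time unresolved. Hence

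intervention / control ratio = (inflow multiplier) / (exit-rate multiplier).

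The documents give neither multiplier. All values here are assumed:

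| Inflow | Exit rate | Ratio |
|---|---|---|
| ×1 | ×2 | 0.50 |
| ×1.5 | ×1 | 1.50 |
| ×1.5 | ×1.5 | 1.00 |
| ×1.5 | ×3 | 0.50 |
| ×2 | ×1.25 | 1.60 |
| ×2 | ×6 | 0.33 |

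The first and fourth rows give the same ratio from a doubling and a tripling of the exit rate. The third row shows no difference although both processes improved by half.

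**4. Size of the detection part alone.** Assume 35% of the list is over 50, so 70,000 × 0.35 / 2 = 12,250 per arm. Assume also that prompted tests are spread over 104 weeks. Extra Group 5 patients present at one search = 12,250 × share extra-tested × yield at or above 11.1 mmol/L × weeks unresolved / 104.

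- Share 10%, yield 0.5%, 8 weeks: 12,250 × 0.10 × 0.005 × 8/104 = 0.5.
- The same with 26 weeks: 1.5.
- The same, never resolved (104 weeks): 6.1.
- Lowest corner (5%, 0.2%, 4 weeks): 0.05.
- Highest corner (20%, 1%, 104 weeks): 24.5.

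The upward push can be negligible or can exceed the control arm's whole expected count of 17.

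**5. Scale of chance variation.** With about 17 expected per arm, the Poisson standard deviation of the difference is about √34 = 5.8 patients.

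**The case against.** The strongest reply is that a randomised comparison of the whole arms is valid for the total effect of the e-Nudge on open high values. A case found and then diagnosed or cleared before the last three searches adds nothing to the numerator. What remains is a raised value without follow-up, which is what the outcome says it measures. Testing itself is credited in the second bullet, on Groups 2 and 6. This stands, and it is why the comparison should be kept. It does not make the result interpretable as resolution, because the number of patients who have something to resolve also depends on the arm.

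A reader might go further and infer that the outcome is biased against the e-Nudge overall. The documents do not support that.

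- Group 5 alerts go to the intervention arm only and speed exit. In the pilot, four of the six patients were confirmed as diabetic, and a fifth had a fasting value of 6.9 mmol/L, which meets the clearing rule.
- Controls are not untested. Usual care continues, and Appendix 3 notes that glucose can be measured at routine blood checks. Only the prompts differ by arm.
- Alerts stop after two years (Outcome analysis), so in year 3 prompting adds no new entries. Cases still open carry over.
- With 8 to 26 weeks unresolved and a 0.5% yield, the push is 0.5 to 1.5 patients, well inside one standard deviation of the difference.

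**Conclusion.** The point holds as one of interpretation. The Group 5 proportion combines prompted detection, which raises it, with prompted resolution, which lowers it, and both are confined to the intervention arm. Taken alone, detection works against the e-Nudge. The net direction is undetermined, because the documents give no extra testing rate, no yield and no time to resolution.

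Its size can only be given as a range: ratios of 0.33 to 1.60 when both processes change, and 0.05 to 24.5 extra patients from detection, against about 17 expected in the control arm. These rest on the pilot rate from one practice, the steady-state simplification and the assumed inputs shown above. A lower proportion would not measure how far resolution improved, a higher one would not show harm, and no difference would not show lack of effect. This concerns one secondary outcome with small counts and leaves the primary outcome untouched.

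**What to change.** Keep the whole-population Group 5 comparison in the third bullet, and describe it as the net backlog of unresolved high values. Add two results:

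- **(a) Resolution.** Among patients in both arms who already met the Group 5 definition from glucose records dated before alerts were switched on, the proportion still unresolved, averaged over the last three searches. Fixing the group by record date matters because alerts run in real time and may precede the first eight-weekly search.
- **(b) Detection.** By arm, over all randomised patients, the number newly entering Group 5 and the number newly added to the Diabetes register.

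Both can come from the practice-database searches that the trial already runs. Control patients' search results are saved, and the algorithm already reads the Diabetes register. The cost is a little more tabulation, including a count of new register entries, which is not one of the six search groups. Result (a) will be imprecise: about 34 patients in all if the pilot rate applies, fewer after deaths and departures. It also leaves out people who join or first qualify later, whom (b) and the retained comparison cover.

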### Statistical analysis

Analysis of the data will be carried out in STATA. The principle analyses will be on an intention-to-treat basis and will be performed using the CONSORT guidelines (2001) [34].

### Data monitoring committee

Outcomes will be assessed annually during the study by an independent data monitoring committee, who will inform the trial investigators if the trial should terminate early on ethical grounds due to a 20% difference in mortality or morbidity between the intervention and control groups.

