### Randomisation

Participating practice patients over 50 years of age will be randomised into two groups – "intervention" and "control." Patients will be consistently allocated to these groups throughout the study using an electronic technique that is concealed to all researchers and practitioners involved. This process will occur electronically during each search, so that those who join the practice during the study will be randomised automatically as soon as they are first provided with electronic notes as a fully registered patient. Temporary residents are not included in the study.

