### Outcome analysis

The searches and alerts will continue for a period of two years, at the end of which the data will be examined. We will continue to collect and analyse data on the primary and secondary outcomes of the study for a further year after this. Outcomes will be measured using searches on practice databases. Analysis will be undertaken on an "Intention To Treat" basis within practices. Practices that withdraw will have their data censored from the date of withdrawal from the trial.

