**Incidence of all cardiovascular events ****1260 per 100,000**

#### Clinical significance

We aim to demonstrate at least a 10% reduction in the cardiovascular event rate. This means that for a positive outcome, the event rate in the intervention population must be ≤90% of the event rate in the control population. We therefore estimated the necessary sample size for this reduction to be detected at the 5% level with 80% power.

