#### Estimating population size needed

A Poisson distribution model is appropriate for events that are rare on an individual level, occurring randomly and independently at a constant rate in a population [37].

Assuming a Poisson distribution, the formula for the sample size is:

where:

λ_0 _= the expected incidence of cardiovascular events (i.e. 1260/100,000)

δ = new incidence in the intervention group

*z*_1-*α *_= standardised normal distribution value based on 0.05 significance level

*z*_1-*β *_= standardised normal distribution values for 80% power

*N *= total number of patients required in the study

*Nw *= total number of patients required in the study + 10% to account for practice withdrawal

For 80% power and 0.05 significance level (2-tailed) [38] (see Table 1):

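### The early-termination criterion is a fixed 20% difference whatever the number of events, so the evidence behind a stop ranges from near noise on few deaths to very strong on many cardiovascular events

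*Protocol article*

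**What the plan says.** The protocol article deals with early stopping only under Data monitoring committee. The schedule is "Outcomes will be assessed annually during the study by an independent data monitoring committee". The committee is to inform the investigators "if the trial should terminate early on ethical grounds due to a 20% difference in mortality or morbidity between the intervention and control groups". The section ties the 20% to no confidence interval, significance level or minimum number of events, and the figure is the same at every look. It does not say whether the 20% is relative or absolute, or which deaths count.

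Under Outcome analysis, "The searches and alerts will continue for a period of two years", and then "We will continue to collect and analyse data on the primary and secondary outcomes of the study for a further year after this". Under Clinical significance the target is stated: "We aim to demonstrate at least a 10% reduction in the cardiovascular event rate". The sample size is set two-sided at 5% with 80% power, using 1260 events per 100,000 per year and a combined all-age list of about 70,000.

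**The concern.** A point-estimate difference is not a measure of evidence. The same 20% can be noise on a small count and far beyond any usual interim boundary on a large one. Mortality and morbidity are joined by an *or*, so either can meet the criterion alone, and the rarer of the two is the noisier.

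Two things are at stake. If deaths are few at the first look, the committee could be led to recommend termination by chance. If events are many at a later look, a difference that is statistically clear but just under 20% would not count under the only criterion written down.

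**Working it through.** **Reading adopted.** 20% is taken as relative, that is, a ratio of 0.8 or below, or 1.2 or above. Read as 20 percentage points, it could not in practice be met at an event rate of about 1.3% per year. Allocation is to two groups (Randomisation: "Participating practice patients over 50 years of age will be randomised into two groups"). The ratio is not stated, so 1:1 is assumed.

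**The plan's own figures.** The trigger has no stated error rate to reproduce. The event rate and population that feed the check do reproduce:
- Rate: 451.77 + 569.77 + 187 + 51 = 1259.54, stated as 1260 per 100,000.
- N = (1.96·√0.0126 + 0.8416·√(0.0126 + 0.00126))² / 0.00126² = 64,133.46, as in Table 1. Times 1.1 this is 70,546.80. (Whether this one-sample form suits the design is a separate matter.)

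**Expected cardiovascular events.** 70,000 × 0.0126 = 882 per year, so about 441 per arm by year 1 and 882 per arm by year 2. This uses the all-age rate on the all-age list. Only patients over 50 are randomised, so the true count is somewhat lower to the extent that events occur at younger ages.

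**Formula.** With e events per arm, SE(log ratio) = √(2/e) and z = ln(ratio)/SE. The chance of meeting the criterion with no true effect is Φ(ln 0.8/SE) + 1 − Φ(ln 1.2/SE). The exact version uses Binomial(2e, 0.5).

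For e = 50: SE = 0.200, ln 0.8/SE = −0.223/0.200 = −1.12 and ln 1.2/SE = 0.182/0.200 = 0.91, so the chance is 0.132 + 0.181 = 0.313.

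| Events per arm | z at 0.8 | z at 1.2 | Null chance, normal | Null chance, exact |
|---|---|---|---|---|
| 50 | −1.12 | 0.91 | 31% | 32% |
| 100 | −1.58 | 1.29 | 16% | 14% |
| 150 | −1.93 | 1.58 | 8% | 9% |
| 200 | −2.23 | 1.82 | 5% | 4% |
| 350 | −2.95 | 2.41 | 1.0% | 1.0% |
| 441 (cardiovascular, year 1) | −3.31 | 2.71 | 0.4% | 0.4% |
| 882 (cardiovascular, year 2) | −4.69 | 3.83 | about 0.01% | about 0.01% |

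The rows from 50 to 350 are assumed death counts; the article gives no death rate. In a simulation of two cumulative annual looks, the chance of meeting the criterion at least once is about 38%, 18% and 5% with 50, 100 and 200 deaths per arm per year.

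**Differences under 20% at year 2.** With e = 882, SE = √(2/882) = 0.0476:
- 16% excess: ln 1.16/0.0476 = 3.12
- 19% excess: ln 1.19/0.0476 = 3.65

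Neither reaches 20%.

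**What |z| > 3 would require.**
- Year 1, e = 441: exp(±3 × 0.0673) = 0.82 or 1.22.
- Year 2, e = 882: exp(±3 × 0.0476) = 0.87 or 1.15.

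**The case against.** The strongest reply is that, for the trial's main outcome, the 20% criterion is already strict. At the planned event rate it corresponds to z of −3.3 or +2.7 at year 1 and −4.7 or +3.8 at year 2, close to or beyond a conventional interim boundary. That stands. A reader might infer that the unadjusted looks leave the type I error on cardiovascular events uncontrolled; null chances of 0.4% and about 0.01% do not support this.

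A reader might also infer that the trial would run on past well-established harm. The figures support less. A 10% excess at year 2 is z = ln 1.10/0.0476 = 2.00, and a 15% excess is 2.94, so neither crosses |z| > 3. Also, the alerts stop at two years, so at that look almost no intervention is left to shorten. At year 1 a 15% excess is only z = 2.08.

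It can be said that a stop for benefit at twice the planned 10% effect must rest on an exaggerated estimate. But |z| > 3 at year 1 also needs an 18% reduction, so this does not separate the two rules.

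Finally, the wording leaves the committee room for judgement, and a charter may add detail. That softens the consequence but does not remove the point: the article does state a criterion, it is the only one given, and a charter that adopted it would inherit the problem. The dependence on assumed deaths is a real limit: at about 350 or more per arm the chance-stop problem is 1% or less.

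**Conclusion.** The point holds as one about a badly fixed criterion. A constant 20% gives a strength of evidence that varies with the count, from |z| of about 1.1 at 50 events per arm to 4.7 at 882. The risk of stopping by chance is confined to deaths and is conditional on their number: about 31-32% at one look with 50 per arm, 14-16% with 100, 8-9% with 150, 4-5% with 200 and 1% with 350. It does not extend to cardiovascular events at the planned rate. The silence on differences under 20% applies to observed excesses of about 16-19% at year 2, and there it bears mainly on reporting and follow-up.

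These figures assume a relative reading, 1:1 allocation, independent events and about 882 cardiovascular events per year. They do not show loss of type I error control on the primary outcome, or continuation past an established 10% excess.

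**What to change.** Replace the raw 20% trigger with a prespecified evidence-based boundary at each annual look, for example Haybittle-Peto with |z| > 3 (two-sided p about 0.003). Apply it to the cardiovascular event rate and to a mortality outcome that the text defines. State the scale of the comparison, keep the committee's discretion to weigh other data, and leave the final test at about 5%.

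The cost is wording in the protocol and the committee's charter. Sample size and data collection do not change, and the effect on the final significance level is negligible.

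There is one downside to acknowledge. At year 1 the boundary needs a ratio of about 0.82 or 1.22 for cardiovascular events, so it is no more sensitive to early harm than the 20% rule. If earlier detection of harm is wanted, a less strict boundary in the harm direction can be prespecified.
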